### **8.12. Unblinding**

In order to maintain the overall quality of the trial, participant-level code breaks will only occur in exceptional circumstances, where the knowledge of the group is clinically essential for the management of the individual.

This risk of this situation is considered to be extremely low given the safety profile of the intervention and therefore it is not expected that this will be necessary during the trial. Where a code break is judged to be essential by the principal investigator, an independent member of the study team (i.e. who will not be undertaking any statistical analyses) will be permitted to unbreak the blinding by accessing the stored dataset.

If a code break occurs, the principal investigator will maintain the blind as much as possible. Whilst the allocation will be known to the participant, in all circumstances, the allocation is not to be disclosed to any other study personnel or the sponsor. The written or verbal disclosure of the code is only to be done where this is clinically necessary. The principal investigator is required to report all code breaks, with the reason for the code break, on an electronic case report file (CRF) page and this must be documented.

## **9. Data Management**

All study data will be electronic and will be obtained from data directly input from the participant. Participant informed consent will be provided electronically. All CRFs and

documentation will be electronic. Paper copies of data or forms will not be held unless they are required in exceptional circumstances (e.g. if CRFs are required by the sponsor); paper copies of documentation will be retained securely in line with standard Northumbria University guidelines.

The online component of the study, and resulting dataset, will be extensively tested prior to the first participant enrolment, to ensure that all methods of data entry are reliable.

The full dataset will be checked and verified for integrity at the end of the study by the principal investigator, and/or other members of the study team. The dataset will also be checked to verify the integrity and quality of data at regular intervals. Any necessary changes to the dataset will be fully documented using a written log.

Anonymised data, and relevant documentation/CRFs will be stored on secure, password-protected computer storage accessible only by the research team. Data will be stored in line with standard university retention guidelines, and will be backed up regularly by Northumbria University IT Services.

## **11. Adverse events**

### **11.1. Definitions**

Adverse event (AE): any untoward medical occurrence in a participant to whom a study intervention has been administered, including occurrences which are not necessarily caused

by, or related to, that intervention. An AE, therefore, does not necessarily have a causal relationship with the intervention. Medical conditions or diseases which are present before starting the study are only considered adverse events if they worsen after the intervention.

**Related AE:** an AE that results from administration from any of the research study procedures. All AEs judged by the principal investigator, or the sponsor, as having a reasonable causal relationship to a study procedure qualify as a related AE. The expression “reasonable causal relationship” means to convey in general that there is evidence or argument to suggest a causal relationship.

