| Probable       | There is evidence to suggest a causal relationship and the influence of other factors is unlikely.                                                                                                                                                                                                                 |
| Definitely     | There is clear evidence to suggest a causal relationship and other possible contributing factors can be ruled out.                                                                                                                                                                                                 |
| Not assessable | There is insufficient or incomplete evidence to make a clinical judgement of the causal relationship.                                                                                                                                                                                                              |

**Unexpected Adverse Event:** An AE that is not listed in the study protocol as an expected occurrence in the circumstances of this trial.

**Serious Adverse Event (SAE):** an untoward occurrence, whether expected or not, that results in death; is life-threatening (referring to an event in which the participant was at risk of death, not an event which hypothetically might have caused death if it were more severe); requires hospitalisation, or prolongation of existing hospitalisation; results in persistent or significant disability or incapacity; is otherwise considered medically significant by the principal investigator. Important medical events that are not immediately life-threatening, or do not result in death or hospitalisation, but that may jeopardise the individual or require

intervention to prevent one of the other outcomes listed above, should also be considered serious.

The severity of all AEs will be graded on a three-point scale of intensity (mild, moderate, severe):

- *Mild*: discomfort is noticed but there is no disruption of normal daily activities
- *Moderate*: discomfort is sufficient to reduce or affect normal daily activities
- *Severe*: discomfort is incapacitating, with an inability to work or to perform normal daily activities. An AE may be severe but not serious.

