### 11.3. Expected adverse reactions

Expected AEs are summarised below. All AEs are expected to be common and well-understood consequences of study participation.

| Procedure                       | Adverse event                          |
|---------------------------------|----------------------------------------|
| Study questionnaires     | Low levels of psychological discomfort |
| Study sleep intervention | Heightened sensitivity to poor sleep   |

As the intervention will be self-administered, participants will be entirely free to discontinue treatment.

For the purposes of this study, any AEs which the investigators are notified of during the study (i.e. from Day 0 to the final study measure) will be recorded. All AEs will be categorised as to expectedness, relatedness and severity.

Serious AEs exclude any pre-planned hospitalisations (e.g. elective surgery) not associated with clinical deterioration; routine treatment or monitoring of the studied indication which is not associated with clinical deterioration; elective or scheduled treatment for pre-existing conditions that did not worsen during the study; serious AEs exclude changes in insomnia severity or sleep, which are already documented within the study.

All AEs will be reported. Any questions concerning AE reporting will be directed to the principal investigator.

*AEs*: all non-serious AEs will be reported using electronic CRFs and sent to the principal investigator as soon as possible. The severity of AEs will be graded on a three-point scale (mild, moderate or severe). The relation (causality) and seriousness of the AE will be assessed by the principal investigator.

*SAEs*: all SAEs will be reported to the principal investigator within 24 hours of the research team learning of its occurrence. The initial SAE report can be made by telephone or e-mail to the principal investigator. In the case of incomplete information at the time of initial reporting, all appropriate information should be provided as follow-up as soon as this becomes available. Relationship of the SAE to study procedures will be assessed by the principal investigator, as should the expected or unexpected nature of the AE. The sponsor does not need to be informed of SAEs.

Evidence of SAEs will trigger a study monitoring meeting, involving the entire research team, to clarify if the trial will need to be discontinued on the basis of these events. The research

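### The adverse event definition leaves out untreated participants and untreated time, conflicts with the recording rule, and no scheduled survey asks about adverse events

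*Combined protocol and SAP*

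**What the plan says.** Section 11.1 limits an AE to "any untoward medical occurrence in a participant to whom a study intervention has been administered". Conditions present before the study are "only considered adverse events if they worsen after the intervention".

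Section 11.3 sets a different scope: "any AEs which the investigators are notified of during the study (i.e. from Day 0 to the final study measure) will be recorded". It adds that "All AEs will be reported", and it names the study questionnaires as a source of an expected event: "Low levels of psychological discomfort". The serious adverse event (SAE) definition, printed under 11.2, opens with "an untoward occurrence, whether expected or not, that results in death" and is not restricted to treated participants.

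On the sponsor, 11.1 treats as related "All AEs judged by the principal investigator, or the sponsor, as having a reasonable causal relationship to a study procedure", whereas 11.3 states: "The sponsor does not need to be informed of SAEs". Section 11.2 gives the causality assignment, and the last word in a disagreement, to the principal investigator.

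Two design features matter here. Good sleepers are randomised to leaflet or no leaflet, and poor sleepers to leaflet or a 28-day wait (8.1, 8.9.3). In the immediate-intervention arms the leaflet follows a week of monitoring (8.9.2, 8.9.3). Section 10 plans no AE summary.

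**The concern.** Harms can be compared between arms only if the same events, over the same time, are counted in the same way in each. The definition in 11.1 starts counting when the leaflet is given. One arm never receives it and another receives it late, so whether an event counts depends on allocation. Two people coding the same complaint could reach different answers, depending on whether they followed 11.1 or 11.3.

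Passive notification adds to this in a trial run entirely online, where no staff visit would bring an event to light.

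The plan gives its own reasons to look. Section 11.3 expects the leaflet to make some people more sensitive to bad sleep and describes expected AEs as common, while section 17 expects no side effects. The leaflet is also given to healthy good sleepers, for whom the balance of benefit and harm matters most.

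**Working it through.** The plan states no AE figure to reproduce, so the check sets the rules side by side and then sizes the gap.

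**1. The two rules applied to the same situations**

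| Situation | Under 11.1 | Under 11.3 |
|---|---|---|
| Any arm, monitoring week before the leaflet | Not an AE | Recorded if notified (window opens at Day 0) |
| Wait-list poor sleeper during the delay | Not an AE | Recorded if notified |
| No-intervention good sleeper upset by a questionnaire | Never an AE | A listed expected AE |
| Pre-existing condition worsens in the no-intervention arm | No time point from which to count | No separate rule |

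The first three rows are direct conflicts. In the fourth, 11.1 refers to a time that the arm never reaches.

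**2. Participants affected**

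Section 8.6 plans 15 per group, 60 in total.
- No-intervention good sleepers: 15/60 = 25%, excluded throughout.
- Wait-list poor sleepers: 15/60 = 25%, excluded until the leaflet.

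**3. Person-time affected**

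Let F be days of follow-up after the leaflet (or the equivalent point) and w the wait-list days before the leaflet. Three months is taken as F = 84 to 91. The wait is taken as w = 28 if counted from Day 0, or 35 if added to the first week. The other three arms have 7 days before the leaflet or the equivalent point. Arms are equal, and dropout is ignored.

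Total per set of four participants = 3(7 + F) + (w + F) = 4F + 21 + w. Time inside the 11.1 definition = 3F.

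| F | w | Inside / total | Outside |
|---|---|---|---|
| 84 | 28 | 252/385 = 0.655 | 34.5% |
| 84 | 35 | 252/392 = 0.643 | 35.7% |
| 91 | 28 | 273/413 = 0.661 | 33.9% |
| 91 | 35 | 273/420 = 0.650 | 35.0% |

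The excluded time is mostly control time. For F = 84 and w = 28 it is 385 − 252 = 133 days: 91 from the no-intervention arm, 28 from the wait-list arm, and 7 from each of the two immediate-intervention arms. No control time in either sleeper stratum lies inside the definition.

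**4. Ascertainment**

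None of the 13 measures in Table 1 is an AE question, and sections 8.9.1 to 8.9.5 describe none. The health questions in Appendix 5 ask about current illness, but Table 1 schedules them at baseline only. The promise in 11.3 to report all AEs covers only events that the team learns of.

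**5. What a comparison could show at this size**

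With 15 per arm and identical definitions (two-sided Fisher exact test at 5%, event rates assumed):
- 30% against 10%: power 0.149
- 40% against 10%: power 0.325
- No events in 15: one-sided 95% upper limit = 1 − 0.05^(1/15) = 0.181

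A formal test would be uninformative; a descriptive table would not.

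**The case against.** The strongest reply is that 11.3 already does the work. It records any notified AE from Day 0 with no limit by arm, relatedness is tied to study procedures generally, and the SAE definition covers everyone. This stands to the extent that a reader should not infer that the control-arm count must be zero. It would be zero only if 11.1 were applied literally, and the plan does not say which rule governs.

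A reader might also infer that the trial cannot assess harm against a control at all. That goes too far. ISI, GAD-7, PHQ-9 and sleep diaries are collected in all four groups and analysed by group in section 10, which also defines a transition to insomnia in good sleepers. Worsening sleep and mood, the harms most relevant to this leaflet, are therefore measured against controls. The gap concerns other events.

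It is tempting to say that SAEs are withheld from the sponsor. Section 11.3 only waives a duty to notify, and section 12 gives the sponsor monitoring, audit and source-data access on request. What remains is that 11.1 gives the sponsor an optional role in judging relatedness while 11.3 does not require it to be told of the serious events it might judge.

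Finally, that AEs are recorded only if participants volunteer them is an inference from the notification wording and the absence of an item. The information sheet and debrief were not available and may explain how to report problems. Even so, they would not make ascertainment active.

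**Conclusion.** The concern holds as a conflict between stated rules, joined to passive collection. Taken literally, the AE definition excludes a quarter of participants throughout, another quarter until their leaflet, and about 34–36% of planned person-time, including all control time. The 25% figures follow from the planned group sizes. The person-time range rests on the assumed follow-up and wait lengths and on no dropout.

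The consequence is limited to AE counts other than the sleep and mood changes measured by ISI, GAD-7, PHQ-9 and the diaries. Those counts would be incomplete and not comparable between arms. The primary analysis is unaffected, and even perfect AE data would not support a formal comparison at 15 per arm. The change is still worth making before recruitment, because control-arm events that are not collected cannot be recovered later.

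**What to change.** - **Definition (11.1).** Define an AE as any untoward occurrence in any randomised participant from Day 0, whatever the arm. Count worsening of pre-existing conditions from Day 0 as well.
- **Collection (Table 1, 8.9).** Add one yes/no item with free text, asking about any new or worse health problem since the last such survey, to the scheduled questionnaire assessments at matched time points in all four groups. Keep it out of the daily diaries: the wait-list arm has an extended monitoring period and an extra Day 28 assessment, and would otherwise be asked more often.
- **Reporting (section 10).** Tabulate AEs descriptively by arm within sleeper status, with wait-list time split before and after the leaflet. Plan no formal test.
- **Sponsor's role.** Reconcile 11.1 with 11.3, so that any part the sponsor has in judging relatedness matches what it is told.

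The cost is one extra survey item per assessment and a little review time for the existing team.

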## 11.2. Causality

The assignment of the causality will be made by the principal investigator using the definitions in the table below. All AEs judged as having a reasonable suspected causal relationship to a study procedure (i.e. definitely, probably or possibly related) are considered to be related AEs. In the case of discrepant views between the principal investigators and others, all parties will discuss the case. In the event that no agreement is made, the principal investigator will make the final decision and both points of view will be documented.

Table 3: explanation of adverse event causality

| Relationship          | Description                                                                                                                                                                                                                                                                                                        |
|-----------------------|--------------------------------------------------------------------------------------------------------------------------------------------------------------------------------------------------------------------------------------------------------------------------------------------------------------------|
| Unrelated      | There is no evidence of any causal relationship                                                                                                                                                                                                                                                                    |
| Unlikely       | There is little evidence to suggest there is a causal relationship (e.g. the event did not occur within a reasonable time after administration of the study procedure). There is another reasonable explanation for the event (e.g. the participant's clinical condition, other concomitant treatment).            |
| Possible       | There is some evidence to suggest a causal relationship (e.g. because the event occurs within a reasonable time after administration of the study procedure). However, the influence of other factors may have contributed to the event (e.g. the participant's clinical condition, other concomitant treatments). |
| Probable       | There is evidence to suggest a causal relationship and the influence of other factors is unlikely.                                                                                                                                                                                                                 |
| Definitely     | There is clear evidence to suggest a causal relationship and other possible contributing factors can be ruled out.                                                                                                                                                                                                 |
| Not assessable | There is insufficient or incomplete evidence to make a clinical judgement of the causal relationship.                                                                                                                                                                                                              |

**Unexpected Adverse Event:** An AE that is not listed in the study protocol as an expected occurrence in the circumstances of this trial.

**Serious Adverse Event (SAE):** an untoward occurrence, whether expected or not, that results in death; is life-threatening (referring to an event in which the participant was at risk of death, not an event which hypothetically might have caused death if it were more severe); requires hospitalisation, or prolongation of existing hospitalisation; results in persistent or significant disability or incapacity; is otherwise considered medically significant by the principal investigator. Important medical events that are not immediately life-threatening, or do not result in death or hospitalisation, but that may jeopardise the individual or require

intervention to prevent one of the other outcomes listed above, should also be considered serious.

The severity of all AEs will be graded on a three-point scale of intensity (mild, moderate, severe):

- *Mild*: discomfort is noticed but there is no disruption of normal daily activities
- *Moderate*: discomfort is sufficient to reduce or affect normal daily activities
- *Severe*: discomfort is incapacitating, with an inability to work or to perform normal daily activities. An AE may be severe but not serious.

### 11.3. Expected adverse reactions

Expected AEs are summarised below. All AEs are expected to be common and well-understood consequences of study participation.

| Procedure                       | Adverse event                          |
|---------------------------------|----------------------------------------|
| Study questionnaires     | Low levels of psychological discomfort |
| Study sleep intervention | Heightened sensitivity to poor sleep   |

As the intervention will be self-administered, participants will be entirely free to discontinue treatment.

For the purposes of this study, any AEs which the investigators are notified of during the study (i.e. from Day 0 to the final study measure) will be recorded. All AEs will be categorised as to expectedness, relatedness and severity.

Serious AEs exclude any pre-planned hospitalisations (e.g. elective surgery) not associated with clinical deterioration; routine treatment or monitoring of the studied indication which is not associated with clinical deterioration; elective or scheduled treatment for pre-existing conditions that did not worsen during the study; serious AEs exclude changes in insomnia severity or sleep, which are already documented within the study.

All AEs will be reported. Any questions concerning AE reporting will be directed to the principal investigator.

*AEs*: all non-serious AEs will be reported using electronic CRFs and sent to the principal investigator as soon as possible. The severity of AEs will be graded on a three-point scale (mild, moderate or severe). The relation (causality) and seriousness of the AE will be assessed by the principal investigator.

*SAEs*: all SAEs will be reported to the principal investigator within 24 hours of the research team learning of its occurrence. The initial SAE report can be made by telephone or e-mail to the principal investigator. In the case of incomplete information at the time of initial reporting, all appropriate information should be provided as follow-up as soon as this becomes available. Relationship of the SAE to study procedures will be assessed by the principal investigator, as should the expected or unexpected nature of the AE. The sponsor does not need to be informed of SAEs.

Evidence of SAEs will trigger a study monitoring meeting, involving the entire research team, to clarify if the trial will need to be discontinued on the basis of these events. The research

team will have access to all data accrued to that point and will have the power to terminate the trial early.

## **12. Data monitoring and quality assurance**

As this is a study with an extremely low risk of side effects due to the behavioural nature of the intervention, a formal Trial Steering Committee, or Data Monitoring Committee, is not required for this study. The trial will be managed and monitored locally by a study management group consisting of the named investigators. Quality control will be maintained through adherence to all relevant Northumbria University standard operating and research governance procedures and the principles of Good Clinical Practice. However, the investigators will permit the sponsor to conduct study-related monitoring, audits and any other inspection, and will provide direct access to source data and study documentation where this is required and requested.

A brief version of this study protocol has already been reviewed by the Northumbria University Department of Psychology ethics committee and ethical approval has been granted (Reference 23377, date of approval: 6 April 2020). All study measures and participant documentation (information sheets, consent forms and debrief forms) have been reviewed and approved by two independent reviewers.

Whilst it is not required, in the interests of transparency, the Northumbria University research ethics committee will be supplied with a copy of the full protocol for reference.

